**Secondary**	
Self-reported data on awareness of the issue, engagement, decisions to act, action, and maintenance	The proportion of respondents who decide to act on precautionary behaviors after a test result for the entire study cohort and stratified by participant demographics (e.g., gender) of interest
Self-reported emergency department visits, hospitalizations, and intensive care unit admission, for SARS CoV-2 evaluation or treatment	Point estimate and 95% confidence interval for each healthcare utilization measure and composite measure for the entire study cohort and stratified by participant demographics (e.g., gender) of interest
Self-reported data on perceptions and prevention of risks of contracting SARS CoV-2 infection	The proportion of respondents who are knowledgeable of precautionary measures to prevent infection for the entire study cohort and stratified by participant demographics (e.g., gender) of interest
Reported results of self-administered SARS CoV-2 antigen test	Prevalence of positive test results with 95% confidence intervals for the entire study cohort and stratified by participant demographic variables of interest
**Exploratory**	
Self-reported data on acceptability, practicality, integration, penetration, and demand of at-home self-administered antigen test	The proportion of respondents who find at-home self-administered antigen test acceptable for the entire study cohort and stratified by participant demographics (e.g., gender) of interest
Mobility patterns as captured by surrogates, including activity trackers	Distribution of individual mobility data in response to positive vs. negative SARS CoV-2 test results
Self-reported data on perceived susceptibility, severity, benefits, barriers, and cues to action related to SARS CoV-2 vaccination	Distribution of respondent’s perception about SARS CoV-2 vaccination for the entire study cohort and stratified by participant demographics (e.g., gender) of interest

##### Sample size and power calculation:

We did not perform a formal power calculation for this observational study. Instead, we anticipated sample size of 5000 participants or 6–7% of the expected 80,000 participants in the public health intervention who take up at-home testing. This sample size will be sufficient to estimate positive test incidence and prevalence, describe behavioral changes associated with test results, and conduct multivariable modeling to understand the causal chain between frequent testing and community burden of disease. For example, if the proportion of participants who adhere to social distancing is 50%, our sample size will be sufficient at a confidence level of 95% to estimate the prevalence with a margin of error of 1.5%.

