##### Sample size and power calculation:

We did not perform a formal power calculation since this is an ecological study. We anticipate that approximately 40,000 households in each intervention community (NC and TN) will participate based on test kit availability. Due to the limited number of intervention communities and only observing outcomes at the community level, there is insufficient power to conduct formal hypothesis tests about the effect of the intervention. Therefore, the proposed analysis is strictly descriptive rather than inferential.

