**Primary**	
Self-reported data on social distancing, quarantine, social connectedness, healthcare utilization, well-being	The proportion of respondents who report adhering to social distancing guidelines after a test result for the entire study cohort and stratified by participant demographics (e.g., gender) of interest; comparison of proportion adherent after positive vs. negative test result

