##### Data analysis plan:

The proposed analysis is primarily descriptive rather than inferential without a priori planned formal hypothesis testing. We designed it to provide a general assessment of participant-level behaviors in a community testing intervention context. An exploratory hypothesis is that positive at-home SARS-CoV-2 antigen test results will lead to altered self-reported social interactions and altered health behaviors compared to negative test results. Demographics, questionnaire data, and testing results will be reviewed and summarized using graphical techniques and summary statistics. Where applicable, we will compute exact method confidence intervals around point estimates, and plot trends over time graphically. We will explore the associations between positive test results and critical behavioral measures using mixed modeling techniques to account for within-participant and within household correlations. SAS 9.4 (SAS Institute, Cary NC) or R 4.0 with R Studio 1.4 (R-project) will be used for statistical analyses.

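### The 1.5-point margin covers whole-cohort proportions only; it does not show that 5,000 participants suffice for the positive-versus-negative comparison or for modelling community burden, and the exact intervals overlook correlation that the plan recognises

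*Protocol article*

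**What the plan says.** All references are to the protocol article.

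- **Behavioral substudy, Sample size and power calculation.** "We did not perform a formal power calculation for this observational study". The size is given as follows: "we anticipated sample size of 5000 participants or 6–7% of the expected 80,000 participants in the public health intervention". The sufficiency claim is unqualified: "This sample size will be sufficient to estimate positive test incidence and prevalence, describe behavioral changes associated with test results". The same sentence extends it to multivariable modelling of the causal pathway from frequent testing to the community's disease burden. One worked example follows: "if the proportion of participants who adhere to social distancing is 50" per cent, then "our sample size will be sufficient at a confidence level of 95% to estimate the prevalence with a margin of error of 1.5" per cent.
- **Table 3, primary endpoint.** There are two parts. The first is the proportion of respondents adhering to social distancing after a test result, for the whole cohort and by demographic group. The second is a "comparison of proportion adherent after positive vs. negative test result".
- **Behavioral substudy, Data analysis plan.** The analysis is mainly descriptive, with no pre-planned formal tests, and the positive-versus-negative hypothesis is called exploratory. For point estimates, where applicable, "we will compute exact method confidence intervals around point estimates". Associations of positive results with behaviour go to mixed models that allow for correlation inside a participant and inside a household.
- **Ecological study, Sample size and power calculation.** With so few intervention communities, and outcomes seen only at community level, power is said to be too low for formal tests of the intervention's effect.

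**The concern.** In a descriptive study, expected precision is the sample-size justification. Here one margin, for one proportion in the full cohort, stands behind a statement that also covers behaviour by test result and a causal model of community burden. The contrast by test result is the substudy's stated hypothesis and part of its primary endpoint. Its precision is governed by the smaller group, the people who test positive in a programme that screens asymptomatic household members. A reader who carries 1.5 points over to that contrast would expect far more than the data can give.

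The second issue is the interval method. The plan recognises correlated records when it models associations, but not when it puts intervals around point estimates. Exact intervals, in the usual sense, treat every record as independent. One or two people test per household (Testing protocol), and questionnaires follow each test (Study questionnaires), so that condition may fail.

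**Working it through.** **Inputs from the article:** n = 5,000; 95% confidence; p = 0.5; stated margin 1.5 points; one or two testers per household. **Not in the article, so assumed:** the share ever positive (1%, 2%, 5%) and the intraclass correlation (ICC) within households (0.2 to 0.8).

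**1. The plan's own figure.** Margin = 1.96 × √(0.25/5,000) = 0.0139, or 1.39 points. The n needed for 1.5 points is 1.96² × 0.25/0.015² = 4,268.3, so 4,269. The example is correct as an upper bound. It leaves room for a design effect of 5,000/4,268.3 = 1.17.

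**2. The positive-versus-negative difference.** Between persons, with p = 0.5 in both groups and no clustering: margin = 1.96 × √(0.25/n₊ + 0.25/n₋).

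| Share ever positive | n₊ / n₋ | 95% margin for the difference (points) |
|---|---|---|
| 1% | 50 / 4,950 | 13.9 |
| 2% | 100 / 4,900 | 9.9 |
| 5% | 250 / 4,750 | 6.4 |
| 50% (best possible) | 2,500 / 2,500 | 2.8 |

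The first three rows are roughly four to nine times 1.5 points. The last row rests on no assumed positivity: no split of 5,000 independent people brings the difference to 1.5 points.

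**3. Household clustering and the whole-cohort margin.** Suppose every participant enrols with one housemate and gives one record. Then the design effect is 1 + (2 − 1) × ICC, and the margin is 1.39 × √(design effect).

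- ICC 0.2: 1.52 points
- ICC 0.5: 1.70 points
- ICC 0.8: 1.86 points

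The margin passes 1.5 points once the ICC exceeds about 0.17, but the change is modest.

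**4. The causal-pathway claim.** Substudy eligibility is limited to residents of the two intervention communities, and the 5,000 are described as a fraction of those who take up testing. Community burden is measured per community. Enrolling more people in the same two communities adds neither communities nor a control community. The ecological section already concedes that the number of communities is too small to test the effect.

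**The case against.** The strongest defence is that nothing stated is numerically wrong. The 1.5-point figure is offered as an example, matches the first part of the primary endpoint, and is never applied to the contrast. The substudy is declared descriptive, its hypothesis exploratory, and the contrast goes to mixed models that handle the correlation. All of this stands, and it makes the fault an overstated justification rather than a failed power calculation. It does not rescue a sentence that says, without qualification, that the sample suffices to describe behaviour by test result.

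A second defence is that people may report negatives before a positive, so a within-person comparison could be more precise. That is true. Take a favourable case with 11 negatives and one positive per person, p = 0.5 and an assumed within-person correlation of 0.7. The variance per person is 0.25 × [1 + (1 + 10 × 0.7)/11 − 2 × 0.7] = 0.082. The margin 1.96 × √(0.082/n₊) is then about 5.6 points for 100 positives and 3.5 for 250, still more than twice 1.5.

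Three stronger readings are tempting, but the article does not support them:

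- **That repeated questionnaires break the 1.5-point margin.** With an assumed 12 per person there are 60,000 records, and the effective number is 60,000/(1 + 11 × ICC), which is never below 5,000. Only household clustering can push the margin up.
- **That the reported intervals will have some specific, badly reduced coverage.** This requires pooling all questionnaires as independent. The article does not say so: its endpoints are mostly framed per respondent, exact intervals apply only where applicable, and the questionnaire schedule is in an additional file not shown.
- **That the uptake percentage is wrong.** 5,000/80,000 = 6.25%, which agrees with the stated range. Elsewhere the article reaches 80,000 by counting households ("We anticipate that approximately 40,000 households in each intervention community (NC and TN) will participate based on test kit availability"), but this loose wording has no bearing on precision.

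**Conclusion.** The point holds in limited form. The 1.5-point margin is sound for a single whole-cohort proportion among independent respondents. It gives no support to the claim that 5,000 is enough to describe behaviour by test result. At assumed positivity of 1% to 5%, the between-person margin for that difference is about 13.9 to 6.4 points, and 2.8 in the best possible case. The claim about modelling the pathway to community burden conflicts with the ecological section's own account of what two communities can show.

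The interval issue is separate and smaller. Exact intervals will be too narrow wherever housemates or several tests from one person enter an estimate. By how much cannot be derived from the article. For the 1.5-point figure itself, pairing within households moves it only to about 1.5 to 1.9 points at ICC 0.2 to 0.8.

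The positivity shares and correlations are assumptions. The 2.8-point bound needs only independence and p = 0.5, the value used in the article's own example.

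**What to change.** - Confine the 1.5-point figure and the sufficiency statement to whole-cohort proportions.
- Add the expected precision of the positive-versus-negative difference over a range of positives, for example 50, 100 and 250, saying whether the comparison is between or within persons.
- Replace exact intervals with cluster-robust (household and participant) or mixed-model intervals wherever people share a household or contribute repeated records. Keep exact intervals for estimates with one independent record per household.
- Remove the claim that the sample suffices to model the causal pathway to community burden.

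The cost is a few sentences and a different interval method. The stated precision becomes less favourable and some intervals slightly wider. No more participants and no new data are needed.

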##### Data analysis plan:

The proposed analysis is primarily descriptive rather than inferential without a priori planned formal hypothesis testing. We designed it to provide a general assessment of participant-level behaviors in a community testing intervention context. An exploratory hypothesis is that positive at-home SARS-CoV-2 antigen test results will lead to altered self-reported social interactions and altered health behaviors compared to negative test results. Demographics, questionnaire data, and testing results will be reviewed and summarized using graphical techniques and summary statistics. Where applicable, we will compute exact method confidence intervals around point estimates, and plot trends over time graphically. We will explore the associations between positive test results and critical behavioral measures using mixed modeling techniques to account for within-participant and within household correlations. SAS 9.4 (SAS Institute, Cary NC) or R 4.0 with R Studio 1.4 (R-project) will be used for statistical analyses.

## Discussion

The SYCT program assesses the impact and behavioral framework of a novel mitigation strategy—rapid, at-home, SARS-CoV-2 testing—implemented through a direct-to-consumer, community-engaged approach that minimizes participant burden and accelerates the translation of test results into daily life. The innovation of this initiative lies in its design, which bypasses the traditional research and healthcare environments and instead brings testing and study procedures to the participants’ homes. This approach minimizes risks by leveraging community engagement and intervention dissemination efforts and maximizes rewards by selectively complementing ecological study data with participant-specific information on behaviors and clinical outcomes associated with frequent at-home testing. In addition, we include both high-tech and low-tech pathways for participants to broaden the accessibility of the intervention and the research study to groups that are traditionally underrepresented.

Implementation and analysis of the SYCT program present significant challenges. The need for rapid deployment of an at-home testing intervention, given the ever-changing and urgent nature of the pandemic, requires the leveraging of local and national resources to employ a broad and multifaceted community engagement strategy. In addition, the use of an ecological study design to assess the impact of the SYCT intervention at the community level limits our ability to conduct formal hypothesis testing; instead, the analysis will be primarily descriptive as opposed to inferential. However, we will maximize our ability to document SYCT’s effect by evaluating an innovative combination of multiple community-level outcomes, using emerging scientific techniques such as wastewater sampling and testing, and analyzing large mobility data sources. In addition, we will be implementing the SYCT program and associated ecological study in an additional two communities before the end of 2021.

Even with the expanding uptake of vaccination, non-pharmaceutical interventions will remain critical components of pandemic control [24]. Therefore, easily accessible, effective testing strategies must be rigorously studied to inform public health policy. The SYCT program will provide critically needed insights into innovative methods to mitigate viral transmission, advance the science of community engagement, and evaluate emerging, novel assessments of community transmission of disease. Our unique, multifaceted approach will allow us to answer questions regarding community transmission for the SARS-CoV-2 pandemic and the socio-behavioral framework of at-home testing relevant to implementing public health interventions for both the current and future pandemics.

## Data Availability

Not applicable.

## Abbreviations

CCPH: Community-Campus Partnerships for Health
CDC: Centers for Disease Control and Prevention
COVID-19: coronavirus disease 2019
NIH: National Institutes of Health
NPIs: non-pharmaceutical interventions
RADx-UP: Rapid Acceleration of Diagnostics–Underserved Populations
SARS-CoV-2: severe acute respiratory syndrome coronavirus 2
SYCT: “Say Yes! COVID Test”
